# Safety and immunogenicity of rVSVΔG-ZEBOV-GP vaccination when dosed concurrent with mRNA COVID-19 vaccine booster doses in healthy African adults (EbolaCov): protocol for a phase IV, single-centre, single-blinded, randomised controlled trial

**DOI:** 10.1136/bmjopen-2025-102898

**Published:** 2025-09-21

**Keywords:** Disease Outbreaks, Clinical Protocols, Immunization Programs, Immunity, INFECTIOUS DISEASES, Vaccination

## Abstract

**Introduction:**

Ebola virus disease remains a significant public health concern. For protection from Ebola virus, the main target populations are epidemiologically identified and often include healthcare workers and refugees. These target populations are also routinely offered vaccines for other vaccine-preventable diseases. However, concomitant use of rVSVΔG-ZEBOV-GP with other vaccines is not recommended, given the absence of data regarding its reactogenicity and antigen-specific immunogenicity profile when co-administered. The EbolaCov trial aims to inform whether rVSVΔG-ZEBOV-GP can be administered concurrent to a Pfizer–BioNTech COVID-19 booster dose without an unacceptable increase in reactogenicity and/or loss of humoral immunogenicity to Ebola vaccine antigen.

**Methods and analysis:**

This is a single-centre, randomised, single-blinded, vaccine safety and immunogenicity study in healthy adults living in Rwanda. Seventy-two participants will be randomised in a 1:1 ratio to two study groups, the first receiving rVSVΔG-ZEBOV-GP with a placebo, the second group receiving rVSVΔG-ZEBOV-GP concurrently with a Pfizer–BioNTech COVID-19 booster dose. The primary outcome measures are quantitative serum anti-glycoprotein (GP) antibody responses, as measured by ELISA, 28 days after vaccination, and frequency and severity of adverse events in the 7 days following vaccination. Secondary outcome measures include day 28 and day 180 serum anti-GP and serum SARS-CoV-2 anti-spike protein-specific geometric mean antibody titres.

**Ethics and dissemination:**

This trial was approved by the Rwanda National Ethics Committee (reference 442/2024) and the University of Birmingham (reference ERN_2661-Jun2024). All participants were required to provide written informed consent in accordance with good clinical practice. Dissemination of results will be through conference presentations and peer-reviewed publications.

**Trial registration number:**

Pan African Clinical Trials Registry (PACTR202407764378004) and ClinicalTrials.gov (NCT06587503)

STRENGTHS AND LIMITATIONS OF THIS STUDYSafety and immunogenicity data following vaccine co-administration will be invaluable knowledge for future outbreaks when conducted in the target population and populations more representative of the settings in which they are needed.The study is statistically powered for non-inferior antibody responses to rVSVΔG-ZEBOV-GP 1 month after vaccination only.This is a single-centre study, which may limit the generalisability of the results.

## Introduction

### Ebola virus and rVSVΔG-ZEBOV-GP vaccine

 Ebola virus was first discovered in 1976, near the Ebola River in the Democratic Republic of the Congo (DRC). Of the four species belonging to the genus *Ebolavirus* that cause disease in humans, Zaire Ebola virus causes the majority of cases, including the largest Ebola outbreak to date between 2014 and 2016. The outbreak started in Guinea before spreading across to Liberia and Sierra Leone, resulting in 28 652 cases and 11 325 deaths over the subsequent 2½ years. The re-emergence of Ebola virus in Africa in 2023 highlights the need for safe, effective and sustained vaccine protection.^1^

The Ebola vaccine rVSVΔG-ZEBOV-GP was licensed by the European Medicines Agency in November 2019 and the United States Food and Drug Administration in December 2019. Countries where this vaccine has been approved for use in include Burundi, Central African Republic, the DRC, Ghana, Guinea, Rwanda, Uganda and Zambia. The Strategic Advisory Group of Experts group recommended the use of rVSVΔG-ZEBOV-GP as part of the coordinated Ebola outbreak control and more than 300 000 people in the DRC were immunised during the 2018–2020 Ebola virus outbreak.^2^ rVSVΔG-ZEBOV-GP is a live-attenuated recombinant vesicular stomatitis virus, Indiana strain, with a deletion of the VSV envelope glycoprotein (GP) and replaced with the Zaire Ebola virus Kikwit 1995 strain surface GP. The standard, licensed rVSV∆G-ZEBOV-GP vaccine dose (1 mL, ≥72 million pfu by intramuscular (IM) injection) will be used in this study. The use of the VSV vector offers multiple advantages, including low seroprevalence of pre-existing vector-specific immunity (supported by the removal of the GP), no host integration of antigen RNA, and ability to accommodate large transgenes. Vaccination with rVSVΔG-ZEBOV-GP provides protection against Ebola virus disease (EVD) caused by the Zaire strain. Primary data analysis from the phase III ring vaccination study, which recruited contacts and contacts-of-contacts of Ebola virus, demonstrated 100% vaccine efficacy against EVD in 2041 subjects who were vaccinated immediately on contact in the 2015 West Africa outbreak and this vaccine has subsequently been used to mitigate further outbreaks in Central Africa.^3^ The vaccine does not confer protection from other species of Ebola virus and the relative contributions towards Zaire strain-specific immunity from innate, humoral and cell-mediated responses are unknown, and defined immune correlates of protection from vaccination or natural infection remain elusive. Data from rVSVΔG-ZEBOV-GP clinical trials has often characterised humoral immune responses using the quantitation of serum IgG-antibody to purified Kikwit ZEBOV GP by validated ELISA (GP-ELISA), which bore close statistical correlation with functional performance of antibody-mediated neutralisation measured by plaque reduction neutralisation titre (PRNT).^4^,^6^ Sero-response criteria have been defined as >2-fold increase in GP-ELISA antibody from baseline and ≥200 EU/mL at any time post vaccination (met by 94% of vaccine trial participants) and ≥4-fold increase from baseline at any time post vaccination by PRNT (met by 80% of vaccine trial participants). A more detailed breakdown of the immunogenicity responses in clinical trials can be seen in the summary of product characteristics document for rVSVΔG-ZEBOV-GP.^7^

### SARS-CoV-2 virus and mRNA vaccines for COVID-19

SARS-CoV-2 is a respiratory virus that emerged in China in November 2019 and a global pandemic was declared on 11 March 2020.^8^ Since February 2022, the Omicron variant has accounted for 98% of clinical isolates and is likely to be the basis for the emergence of further SARS-CoV-2 variants.^9^ To date, there have been 766 million confirmed cases of SARS-CoV-2, 6.9 million confirmed deaths and 13.4 million vaccine doses administered worldwide.^10^ Moderna and Pfizer–BioNTech manufactured messenger RNA (mRNA) COVID-19 vaccines were the commonly used products in the global effort to vaccinate against SARS-CoV-2.^11^ Comirnaty (Pfizer–BioNTech) encodes for full length spike protein with two-point mutations to proline in the central helix to lock spike into the prefusion conformation. Clinical trials of Comirnaty reported a good safety profile and vaccine efficacy of 95% in one clinical trial where 21 720 participants received the vaccine.^12^

### Rationale for the proposed study

Vaccines for the prevention of severe disease caused by Ebola virus and SARS-CoV-2 virus are routinely offered to adults at higher risk of exposure in the African settings. For protection from Ebola virus, the main target populations are epidemiologically identified and include healthcare workers, refugees and people living in outbreak zones. These target populations are also routinely offered vaccines for other vaccine-preventable diseases. However, there are currently no data on whether the co-administration of rVSVΔG-ZEBOV-GP with other vaccines has an acceptable profile of reactogenicity and antigen-specific immunogenicity, and concomitant use of rVSVΔG-ZEBOV-GP with other vaccines is not recommended. Clinical trial data on the co-administration of rVSVΔG-ZEBOV-GP with other vaccines prioritised for the same population, and especially in the context of a new era in mRNA vaccine technology, would have significant relevance to how protection from other diseases can be provided at a single clinic visit alongside the rVSVΔG-ZEBOV-GP vaccine. This, in turn, has the potential to improve vaccine coverage, the efficiency of vaccine policy and logistics, as well as being the first step in the evaluation of VSV-vectored vaccine technology with lipid-enveloped mRNA platforms that are going to be increasingly used in other formulations against other/future infectious disease targets.

### Significance of selected topic

There are no preliminary data in this first-of-kind study. The advent of the SARS-CoV-2 virus and COVID-19 pandemic signalled the accelerated development of lipid-nanoparticle mRNA vaccine technology with great success. The mRNA platform is highly adaptable to new disease targets, including cancer and infectious disease pathogens, and a multitude of vaccine candidates are currently in development for outstanding global health priorities that have eluded pre-pandemic technologies. However, very little is known about using mRNA technologies in combination with, or concurrent to, other vaccine technologies and whether there are any adverse signals associated with safety or antigen-specific immune response/protection. We are only now beginning to answer this important data gap. Earlier trials have focused on using SARS-CoV-2 mRNA vaccines in combination with adjuvant protein vaccines for seasonal influenza (and herpes zoster virus, in setup) and have reported favourable safety and humoral immune responses. This has resulted in the recommendation to include the concurrent vaccine dose administration within the annual seasonal vaccination schedule of UK nationals.^13^ These study data have significantly supported public confidence in accepting two licensed vaccines at the same time, and significant efficiency gains in vaccine coverage and public protection. The concurrent administration of mRNA vaccines with attenuated or replication-incompetent viral-vectored vaccines has not, to our knowledge, been assessed although many trials reported favourable safety and immunogenicity with heterologous combinations of these vaccine platforms for protection against COVID-19.^14^,^16^ Since existing mRNA COVID-19 vaccines and new mRNA constructs against other infectious diseases are expected to become routine immunisations for key members of the population, such as healthcare workers and older adults, research is needed to inform whether concurrent or co-administration with other vaccines is possible. For African populations, the risk of disease outbreaks from Ebola remains high and the future use of rVSVΔG-ZEBOV-GP is expected, along with other measures, to mitigate the risks to healthcare workers and the wider public. Assessing the safety and immunogenicity of rVSVΔG-ZEBOV-GP vaccine in the context of expected gains in public confidence and policy implementation with co-administration with mRNA vaccine technologies is a major subject of interest for African populations and preparedness for future disease outbreaks.

## Methods and analysis

We used the Standard Protocol Items: Recommendations for Interventional Trials checklist when preparing the present protocol report.^17^

### Trial design and setting

This is a single-centre, randomised, participant-blinded, vaccine safety and immunogenicity study in healthy adults living in Rwanda. The EbolaCov trial aims to inform whether the Ebola vaccine rVSVΔG-ZEBOV-GP can be administered concurrent to a Pfizer–BioNTech COVID-19 booster dose without an unacceptable increase in reactogenicity and/or loss of humoral immunogenicity to Ebola vaccine antigen.

This trial is being conducted at the research and healthcare facility the Center for Family Health Research in Kigali, Rwanda, in collaboration with Rwanda Biomedical Centre, the national central health implementation agency for Rwanda.

### Objectives and outcomes

The primary safety objective is to determine the frequency and severity of severe solicited systemic adverse reactions within 1 week of concurrent vaccine dose administration, compared with giving the rVSVΔG-ZEBOV-GP vaccine alone. Participant-reported reactogenicity data will be entered via an e-diary or a backup paper diary. Data includes solicited adverse events (AEs), including injection site reactions (pain, tenderness, erythema, swelling, axillary swelling or tenderness), as well as systemic symptoms (headache, malaise, myalgia, nausea, vomiting and fever). AEs of special interest include arthritis, synovitis, joint effusions, temporomandibular joint syndrome, tendonitis, mucosal or skin lesions and postvaccination dermatitis. All AEs will be graded in severity by the participant and then reviewed by the study team. Relationship to the trial vaccines will be determined by a study physician.

The primary immunogenicity objective is to measure serum anti-GP antibody responses 28 days after concurrent vaccine dose administration, compared with giving the rVSVΔG-ZEBOV-GP vaccine alone. This outcome will be measured using day 28 serum anti-GP antibody responses assessed by commercially available ELISA.

Secondary objectives include longitudinal assessment of humoral response to rVSVΔG-ZEBOV-GP and SARS-CoV-2 when co-administered with Pfizer–BioNTech COVID-19 booster vaccination, compared with giving the rVSVΔG-ZEBOV-GP vaccine alone, and assessment of SARS-CoV-2 anti-spike protein specific geometric mean titres (GMT) when co-administered with rVSVΔG-ZEBOV-GP vaccine. Secondary immunogenicity outcome measures include day 28 and day 180 anti-GP and anti-spike GMT measured by commercially available ELISA.

We also aim to evaluate the perceptions and acceptability of concurrent vaccination among healthcare workers and volunteers who took part in the study using transcripts from semi-structured interviews (or focus groups) conducted for this purpose.

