### Statistical analysis plan

Analyses of both the intention-to-treat and per-protocol populations will be presented. Statistical analyses will be descriptive in nature (counts/proportions, or GMT where appropriate). Any comparative statistics (χ^2^/Fisher’s-exact or paired/unpaired t-test where appropriate) and analyses of exploratory/longitudinal data will be post-hoc analyses.

The full details of the analysis will be provided in the statistical analysis plan which will be finalised prior to unblinding and database lock.

Interview transcripts will be analysed qualitatively.

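### The primary safety outcome is defined in two ways, and the version in the body leaves room for staff not stated to be blinded to influence which events count

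*Protocol article*

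**What the plan says.** **Outcome.** The Abstract (Methods and analysis) gives the primary safety outcome as "frequency and severity of adverse events in the 7 days following vaccination". The body (Objectives and outcomes) states the primary safety objective as to "determine the frequency and severity of severe solicited systemic adverse reactions within 1 week of concurrent vaccine dose administration".

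**Data and judgement.** The same body section says: "Participant-reported reactogenicity data will be entered via an e-diary or a backup paper diary". It then says: "All AEs will be graded in severity by the participant and then reviewed by the study team". On causality it says: "Relationship to the trial vaccines will be determined by a study physician".

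**Blinding.** The Abstract calls the trial single-blinded. Trial design and setting is more specific: "This is a single-centre, randomised, participant-blinded, vaccine safety and immunogenicity study in healthy adults living in Rwanda". No section states whether the grade reviewers or the study physician are masked. The analysis section refers to a "statistical analysis plan which will be finalised prior to unblinding and database lock", without saying who remains blinded until then. Table 1 lists unblinding at day 180.

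**The concern.** The two definitions differ in a way that affects bias. An adverse event is counted whatever its cause. An adverse reaction, in its usual sense, is an event judged related to the vaccine, so a count of reactions can depend on someone's causality call. The body's wording also restricts the outcome to severe events, which makes the grade decisive.

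Both attributes, severe and reaction, are handled by study staff after the participant has reported. The participant is protected by a saline placebo injection. The staff have no stated protection. Most of the listed systemic symptoms (headache, malaise, myalgia, nausea) are subjective. Someone who knows that a participant received two active vaccines might call such a symptom related or severe more readily than in the placebo group, or less readily if expecting a benign profile. A between-group difference could then be created or hidden by assessment. The comparison of reactogenicity is one of the trial's two primary questions, and it will rest on small descriptive counts.

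**Working it through.** The plan gives no figure on this point to reproduce. The check is a comparison of texts, followed by an illustration of scale.

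**1. The two definitions side by side**

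| Feature | Abstract | Objectives and outcomes |
|---|---|---|
| Unit counted | adverse events | adverse reactions |
| Restriction | none stated | severe, solicited, systemic |
| Window | 7 days | 1 week |
| Could a causality call decide inclusion? | no | yes, if reaction means judged related |
| Could the severity review affect it? | yes, severity is reported | yes, severity decides inclusion |

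**2. Who acts on each attribute**

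- Occurrence of the symptom: the participant's diary (blinded).
- Severity: the participant first (blinded), then study-team review (masking not stated).
- Relatedness: a study physician (masking not stated).

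The article does not say that the participant's grade is final, or that solicited events are counted whatever their assigned cause. Under the Abstract's wording only the severity route is open. Under the body's wording both may be.

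**3. Scale of a reclassification**

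Input: 36 per arm (Sample size).

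- One participant: 1/36 = 2.8 percentage points on that arm's rate.
- Three participants in one arm: 3/36 = 8.3 points.
- For comparison, assume 2 events in each arm. The Wilson 95% limits for 2/36 = 5.6% are 1.5% and 18.1%. The Newcombe half-width for the difference is √[(5.6 − 1.5)² + (18.1 − 5.6)²], which is 13.2 points from unrounded values.

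Three such calls therefore move the estimate by less than its sampling uncertainty, but the interval makes no allowance for that shift.

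**4. Scale of differential attribution**

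The document gives neither an event rate nor an attribution rate, so both are assumed. Let the true rate p of severe solicited systemic events be equal in both arms, with 100% called related in the co-administration arm and a fraction s in the placebo arm.

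- Observed risk ratio = p / (p × s) = 1/s.
- Observed risk difference = p × (1 − s).

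| s | Risk ratio | Difference, p = 10% | Difference, p = 20% | Difference, p = 30% |
|---|---|---|---|---|
| 0.9 | 1.11 | 1 point | 2 points | 3 points |
| 0.8 | 1.25 | 2 points | 4 points | 6 points |
| 0.7 | 1.43 | 3 points | 6 points | 9 points |

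At p = 20% the expected counts are 36 × 0.20 = 7.2 in the co-administration arm, against 6.5, 5.8 or 5.0 in the placebo arm. If attribution is the same in both arms, the ratio is 1. If events are counted regardless of causality, s does not enter and this route contributes no bias.

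**The case against.** The case against has four parts.

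- **Causality as a filter is not stated.** No sentence says the outcome counts only events judged related. The Abstract's version needs no such call, and the body uses event and reaction loosely: its list of solicited adverse events includes injection site reactions. The causality sentence may describe general adverse-event handling. This stands. Filtering on causality is one permitted reading, not the plan's stated rule.
- **Review need not mean override.** It could be a check for completeness and plausibility. This also stands.
- **The assessors' masking is unknown.** The reference to finalising the analysis plan before unblinding, and the statement under Governance that the data safety monitoring committee sees unblinded data, are compatible with some staff staying masked. This stands as far as it goes. Neither passage names the reviewers or the physician, and the day-180 entry in Table 1 fits unblinding of participants equally well.
- **The consequences are limited.** Safety analysis is descriptive, the trial is powered only for the day-28 antibody response, participants grade first, and the reclassification figures are hypothetical. All true, and all reasons to keep the point in proportion.

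A reader might infer that unblinded staff will regrade events and decide which ones enter the primary outcome. The document does not support that, for the first three reasons. What the objection does not remove is the disagreement between the two definitions, both of which are stated. Nor can it be answered only by deferring to documents not shown: they may add detail on masking, but the article's two statements of the outcome still have to be reconciled.

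**Conclusion.** The primary safety outcome is stated inconsistently, and the body's version permits staff who are not stated to be blinded to influence inclusion through severity and relatedness. This is a possible bias, not a demonstrated one. It needs three things to be true together: the assessors know the allocation; their grade or causality call decides what is counted; and those calls differ between arms. The document establishes none of the three and excludes none.

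Its size cannot be estimated from the document. The illustrations give 2.8 points per reclassified participant in an arm and, under assumed attribution gaps of 10% to 30%, spurious risk ratios of 1.11 to 1.43. The point is worth acting on because a better rule is available from data already being collected.

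**What to change.** Reconcile the Abstract with Objectives and outcomes, and use one definition throughout: any solicited systemic event within 7 days of vaccination that the blinded participant grades as severe in the diary, counted regardless of assigned causality. Report the team-reviewed grade and the physician-assigned relatedness as secondary or sensitivity results. Leave safety review and causality assessment of serious adverse events as they are.

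This takes both routes out of the primary comparison, whatever the masking of staff turns out to be. It costs one sentence in the protocol and analysis plan, plus one extra table, with no new staff, visits or data. The small downside is that some unrelated or over-graded events will be counted. With randomised arms and blinded reporting these should fall on both arms alike in expectation, so they may pull a risk ratio towards 1 but should not favour either arm. The analysis plan is to be finalised before unblinding, so the definition can be fixed there first.

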### Recruitment and eligibility

We aim to primarily recruit participants who are current healthcare workers, although the study will be open to all eligible members of the public. Study participants will be self-selected individuals responding to invitations to consider taking part. Recruitment/engagement will include staff email contact, conference/meeting presentations and other methods using Rwanda National Ethics Committee (RNEC) approved methods and materials. A total of 72 participants is required. Participants must be able to consent, healthy, aged 18–50 years, and should have already received a WHO approved primary COVID-19 immunisation course for inclusion into the study.

Participants will receive information via an RNEC-approved study information booklet (SIB) followed by a discussion with trained study staff, who will then gain informed consent. The SIB is available in both English and Kinyarwanda, the national language of Rwanda, and the informed consent discussion will be in the language of choice of the participant. Witnessed consent with a thumbprint as confirmation of consent will be available for illiterate individuals. RNEC-approved copies of the SIB and informed consent form are available in the online supplemental material (English and Kinyarwanda versions). Eligibility will be assessed during the screening visit based on medical and vaccination history, physical examination, vital signs and pregnancy and HIV point-of-care testing. Demographic data will also be collected at this point.

Eligibility criteria broadly reflect the summary of medicinal product characteristics for the licensed rVSVΔG-ZEBOV-GP vaccine and the emergency use authorisation requirements for the Pfizer–BioNTech vaccine when used to control the recent COVID-19 pandemic. These are outlined in figure 1. Exclusion criteria include any condition that may impair the immune response to vaccination or would mean receipt of either vaccine would be high risk for the participant (figure 1). Enrolment may be delayed if temporary exclusion criteria likely to bias the results are met (figure 1).

